## Abstract

Individuals who have suffered a severe brain injury typically require extensive hospitalization in intensive care units (ICUs), where critical treatment decisions are made to maximize their likelihood of recovering consciousness and cognitive function. These treatment decisions can be difficult when the neurological assessment of the patient is limited by unreliable behavioral responses. Reliable objective and quantifiable markers are lacking and there is both (1) a poor understanding of the mechanisms underlying the brain’s ability to reconstitute consciousness and cognition after an injury and (2) the absence of a reliable and clinically feasible method of tracking cognitive recovery in ICU survivors. Our goal is to develop and validate a clinically relevant EEG paradigm that can inform the prognosis of unresponsive, brain-injured patients in the ICU. This protocol describes a study to develop a point-of-care system intended to accurately predict outcomes of unresponsive, brain-injured patients in the ICU. We will recruit 200 continuously-sedated brain-injured patients across five ICUs. Between 24 h and 7 days post-ICU admission, high-density EEG will be recorded from behaviorally unresponsive patients before, during and after a brief cessation of pharmacological sedation. Once patients have reached the waking stage, they will be asked to complete an abridged Cambridge Brain Sciences battery, a web-based series of neurocognitive tests. The test series will be repeated every day during acute admission (ICU, ward), or as often as possible given the constraints of ICU and ward care. Following discharge, patients will continue to complete the same test series on weekly, and then monthly basis, for up to 12 months following injury. Functional outcomes will also be assessed up to 12 months post-injury. We anticipate our findings will lead to an increased ability to identify patients, as soon as possible after their brain injury, who are most likely to survive, and to make accurate predictions about their long-term cognitive and functional outcome. In addition to providing critically needed support for clinical decision-making, this study has the potential to transform our understanding of key functional EEG networks associated with consciousness and cognition.

## Introduction

Individuals who have suffered a severe brain injury typically require extensive hospitalization in intensive care units (ICUs) to survive their injury and regain their cognitive functions. In the acute stage post-injury, the decisions made by the ICU healthcare teams have an enormous impact on patient survival and outcomes. Importantly, decisions regarding the treatment course and goals of care are often based on behavioral responses, which are highly dependent on a multitude of clinical and environmental factors, rather than on objective and quantifiable markers. There is thus a critical need to develop systems and techniques that can be deployed at the bedside to predict patient outcome, and thus inform clinical decision-making about treatments of unresponsive brain-injured patients in the ICU.

There are two major barriers to developing and deploying a point-of-care system for predicting outcomes of brain-injured patients. First, there is currently no accepted set of robust prognostic markers that can be gathered at the bedside when patients are unresponsive. Though fMRI is an attractive option, most patients are too vulnerable within the first days post-admission to be moved to the fMRI scanner (Weijer et al., 2016). While the brain responses of these patients are routinely monitored through electroencephalography (EEG) and visually inspected by a trained neurologist to identify pathological characteristics, the EEG waveforms and spectral properties have limited prognostic value with respect to cognitive outcomes, beyond predicting patient survival. Second, very little is known about the long-term outcomes of ICU survivors. While it is known that long-term cognitive impairments affect 40–100% of ICU survivors (Hopkins et al., 2005; Moulaert et al., 2009; Iwashyna et al., 2010; Wilcox et al., 2013; Honarmand et al., 2020), and affects people of all ages (Pandharipande et al., 2014), there is a lack of a systematic, patient-accessible method for accurately tracking cognitive recovery in these patients. Our group has recently established that a web-based cognitive battery that can be self-administered by patients is both feasible for use in ICU patients and accurately detects cognitive impairment across multiple cognitive domains (Honarmand et al., 2019). In the absence of this cognitive recovery data, it is impossible to characterize the prognostic value of any markers gathered in the ICU from this population.

In current clinical practice, predictions of outcome in brain-injured patients vary based on the etiology of coma. Demographic data, history, brainstem examination, behavioral measures, and motor responses (e.g., Glasgow Coma Scale) (Teasdale and Jennett, 1974), electrophysiology (EEG, somatosensory evoked potentials), and neuroimaging findings are all considered. Though these measures are accessible, some have a contested prognostic value, especially within the first days post-injury (Kouloulas et al., 2013). Brain responses gathered through EEG have shown some promise in predicting outcomes in this population. In particular, the presence of the mismatch negativity (MMN) event-related brain potential (ERP) has been associated with awakening from a state of coma (Fischer et al., 1999; Morlet and Fischer, 2014). While the presence vs. absence of this brain response has high specificity (>90%), it has an extremely low sensitivity (<30%), and thus has limited value in clinical practice. Other long-latency ERPs such as the P300 and N400 have also been tested for prognostic purposes but have shown poor sensitivity and specificity (Wang et al., 2011).

Preliminary studies from our team have suggested the potential prognostic value of network features of continuous EEG and the reorganization of these features upon a change of sedation/anesthesia status (Blain-Moraes et al., 2017; Nadin et al., 2020). Instead of focusing on waveforms and spectral properties (as measured in clinical EEG) or on event-based responses, information flow networks in the brain (e.g., functional connectivity and graph properties) and their changes upon administration or removal of anesthesia have heralded the return (or not) of patient consciousness. These network-based features of EEG have also shown positive predictive values of an unresponsive individual’s level of consciousness in patients exposed to anesthesia, in other recent studies (Boly et al., 2011; Lee H. et al., 2013; Lee U. et al., 2013; Chennu et al., 2016). While promising, the full prognostic potential of these features have yet to be explored.

The use of EEG network features as a prognostic tool must be validated against a set of patient outcome measures that are sensitive to the dynamic and complex changes in cognitive functions across multiple domains in ICU survivors. Such measures have historically been difficult to gather due to a lack of comprehensive, easy-to-administer neurocognitive tests. Currently, assessment of cognitive function requires that patients attend a clinic where specially trained personnel administer standard cognitive batteries. This model has several limitations including the length of these testing sessions, patient inconvenience of traveling to clinic assessments, high costs associated with employing trained personnel, and high rates of patient attrition. As a result, traditional methods of comprehensive cognitive assessment cannot be used for a large-scale multi-center natural history study that requires repeated measurement of cognitive function within individual patients during their recovery (Honarmand et al., 2020).

Over the last 25 years, a suite of computerized cognitive tests, named Cambridge Brain Sciences (CBS), has been developed to assess aspects of memory, attention, planning and reasoning in healthy adults and patient populations (Owen et al., 1990, 1991, 1992, 1996, 2010; Bor et al., 2003; Hampshire et al., 2012). The CBS tests have been validated in patients with anatomically-specific brain lesions (e.g., Owen et al., 1990, 1991), in neurodegenerative populations (e.g., Owen et al., 1992, 1993), in pharmacological intervention studies (e.g., Lange et al., 1992; Mehta et al., 2000), and their neural correlates have been well-studied using functional neuroimaging in healthy adults (e.g., Owen et al., 1996), and in neuropathological populations (e.g., Owen et al., 1998; Williams-Gray et al., 2007). Recently, the tests were adapted to run online without formal supervision, opening the possibility of large-scale studies of cognition in the general population (Hampshire et al., 2012; Wild et al., 2018). In a recent pilot study (Honarmand et al., 2019), this cognitive battery of tests, called Cambridge Brain Sciences (CBS), was used in a cohort of ICU patients, found that it is both feasible to self-administer and able to identify cognitive impairments in several domains. The CBS tests have now been taken more than 10 million times, generating one of the largest databases of its kind in the world. Crucially, this includes a normative database of 75,000 participants. These statistics demonstrate that web-based studies of cognition are not only possible, but provide a novel opportunity for assessing the multitude of factors that contribute to healthy cognition on a scale that would be simply impossible using traditional laboratory-based methods.

By bridging the gap between novel high-density EEG markers and rigorous, long-term tracking of cognitive recovery, the current study aims to design a point-of-care system that predicts neurological outcomes of continuously-sedated, brain-injured patients in the ICU. More specifically, we aim to identify EEG markers that can be recorded at the ICU bedside, which (1) capture network reorganization upon the change of sedation (i.e., during a brief interruption of continuous sedation), and (2) robustly predict recovery of consciousness and cognition up to 12 months post-injury. To attain this objective, we will carry out high-density EEG recordings between 24 h and 7 days post-ICU admission on continuously sedated brain-injured patients before, during and after a brief interruption of continuous sedation. Patients who subsequently regain consciousness will be asked to complete an abridged CBS battery on a daily basis during the hospital stay and on a weekly basis up to 3 months following the recovery of consciousness (i.e., start of CBS testing). Testing will continue on a monthly basis until 12 months post-injury.

Findings from this study will have important implications for our understanding of how the functional EEG networks that may underlie consciousness and cognition are disrupted by injury, and how these networks drive recovery. Ultimately, this study has the potential to improve clinical decision-making and prognostication of unresponsive, brain injured-patients, within the first days post-injury.

## Materials and Equipment

This study requires a high-density EEG system comprising a minimum of 64 channels, headphones, and a tablet or laptop computer with Internet access.

### Methods

#### Ethics and Study Design

This multi-center study was reviewed and approved by the Research Ethics Board of the McGill University Health Centre (Project ID 2020-5972) and the Western University Health Science Research Ethics Board (Project ID 114303). Given that research participants are unable to consent to their participation in the study given the sudden nature of their injury or medical condition, written informed consent will be provided by a family member (next of kin) in accordance with the Declaration of Helsinki.

#### Participants

Two hundred (*n* = 200) brain-injured patients in a pharmacologically-induced coma will be recruited from three ICUs in Montreal, QC, Canada (the Montreal General Hospital, the Montreal Neurological Hospital, the Royal Victoria Hospital) and two ICUs in London, ON, Canada (University Hospital and Victoria Hospital). Sample size was determined based on feasibility (i.e., number of patients in this condition per ICU on a yearly basis, estimated patient survival rates) and the fragile medical state of our study population. Considering that several patients may not survive their injury and/or may withdraw from the study prior to the 12-month follow-up, we aim to have 200 patients initially included in order to have 100 patients complete the entire study (up to 12 months post-injury).

Patients will be included if they have suffered a brain injury (e.g., traumatic brain injury, anoxic brain injury, stroke, subarachnoid hemorrhage); are continuously sedated; are between 24 h and 7 days post-injury; are aged between 18 and 70 years of age; and have a planned interruption of sedation for clinical assessment. Patients will be excluded if: they are not native English or French speakers; they are deemed medically unsuitable by the attending physician; there are barriers to appropriate application of the high-density EEG net (e.g., scalp infections, burns); they have a history of pre-existing dementia or mild cognitive impairment; they show presence of *status epilepticus*; they are on contact precautions (e.g., methicillin-resistant *Staphylococcus aureus*, COVID-19), which require an extraordinary disinfection protocol for testing equipment.

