##### EEG recording 2 – interruption of sedation

Sedation will be stopped, and clinicians will conduct their clinical neurobehavioral assessment, as per standard of care. The EEG net will remain on the participant’s head during this time. Once sedatives have been withheld and the clinical neurobehavioral assessment has been completed, participants will remain without sedation for a maximum of 15 additional minutes – or as long as the patient is tolerating it and the medical team deems it safe [i.e., vitals remain stable and intracranial pressure remains normal (<20 mmHG)] – during which brain activity will be recorded with EEG for the study. Of these 15 min of EEG recording, 5 min will be recorded at resting state and 10 min will be recorded while the patient is listening to an auditory narrative intended to evoke evidence of higher cognitive functioning, including covert awareness (Naci et al., 2017). We will use the auditory narrative paradigm to look for evidence of covert awareness during the interruption of continuous sedation. Patients will have headphones placed over their ears for 10 min while EEG is recorded during the interruption of sedation. We will play a 5-min scrambled audio segment of the motion picture *Taken*, and subsequently play the unscrambled audio of the same 5-min segment.

As patient safety will be prioritized, sedatives will be reinstated as standard of care after the 15 min of EEG recording, or as soon as the clinical team decides to do so, whether or not the EEG recording is complete.

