## Discussion

This study is designed to develop a point-of-care system that can accurately predict outcomes of unresponsive, brain-injured patients in the ICU. This system will combine (1) advanced techniques in EEG network analysis with (2) a web-based battery of cognitive tests for long-term assessment of cognitive recovery in ICU survivors, to create a method of accurately predicting patient prognosis and long-term outcomes.

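### The stated use is prognosis in unresponsive patients, but patients who follow commands once sedation stops can be enrolled and are pooled with the rest in the classifier analyses

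*Protocol article*

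**What the plan says.** **Intended use.** The Abstract, Introduction and Discussion describe a tool for unresponsive patients. The Discussion gives the purpose as to "develop a point-of-care system that can accurately predict outcomes of unresponsive, brain-injured patients in the ICU". The Abstract adds that "high-density EEG will be recorded from behaviorally unresponsive patients before, during and after a brief cessation of pharmacological sedation".

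**Eligibility.** Under Participants, "brain-injured patients in a pharmacologically-induced coma will be recruited". The inclusion items that bear on the patient's state are that they "are continuously sedated; are between 24 h and 7 days post-injury" and that they "have a planned interruption of sedation for clinical assessment". The other items are brain injury and age 18 to 70. None of the exclusions concerns behavior off sedation.

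**Sequence at the bedside.** In the section on EEG recording 2: "Sedation will be stopped, and clinicians will conduct their clinical neurobehavioral assessment, as per standard of care". The study recording starts "Once sedatives have been withheld and the clinical neurobehavioral assessment has been completed". The section has no rule for a patient who is found responsive.

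**Analysis.** The section on acute EEG features and patient outcomes uses EEG reconfiguration and plot following at the interruption to classify recovery of consciousness, survival, and levels of cognitive and functional recovery. The section on demographic and clinical characteristics uses GCS at admission and visual fixation at 24 h, each in its own regression. The Discussion plans subgroups by injury type only.

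**The concern.** Under continuous sedation a patient may be unresponsive because of the drug alone. Entry by sedation status therefore does not separate patients who remain unresponsive without the drug from those who wake when it is stopped.

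The predictor is the EEG change from the sedated to the unsedated phase. Anticipated Results expects feedback-dominant frontoparietal connectivity and posterior alpha hubs to reappear in patients who recover. A patient who is awake at the interruption would be expected to show such changes too, and is also more likely to be counted later as having recovered consciousness. In a pooled analysis, a feature that only detects present wakefulness can thus score as prognostic.

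At stake is whether the accuracy applies to the patients for whom the tool is meant. The Introduction says that treatment and goals-of-care decisions need better support than behavioral responses give. If a patient already follows commands, the bedside examination has shown this without EEG.

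**Working it through.** **Step 1: the criteria against the aim.** Every listed criterion is met by a patient who obeys commands as soon as sedation is off. The Abstract's description of behaviorally unresponsive patients shows intent, but it is not carried into the criteria.

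**Step 2: order of events.** Sedation is stopped, the clinical assessment is done, then Recording 2 begins. Responsiveness is therefore known before the key EEG.

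**Step 3: whether a later step repairs the gap.** The classifier section neither restricts to nor stratifies by the assessment result. The regressions do not use responsiveness at the interruption. The within-subject argument in the Discussion does not help, because the within-subject EEG change is itself the predictor.

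**Step 4: how large the effect could be.** The article states no accuracy figure to reproduce. Its sample size is feasibility-based and consistent with about 50% completing (100 / (1 − 0.5) = 200); the point does not depend on it. All inputs below are assumptions.

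*Upper-bound illustration, recovery of consciousness only.* Let f be the share responsive at the interruption and p the recovery rate among unresponsive patients. Assume that the EEG detects responsiveness perfectly, has no prognostic value in unresponsive patients (AUC 0.50), and that all responsive patients recover. The share of recovered patients who were responsive is r = f / (f + (1 − f)p), and the pooled AUC = r + 0.5(1 − r).

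With p = 0.4:

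| f | r | pooled AUC |
|---|---|---|
| 10% | 0.10/0.46 = 0.217 | 0.61 |
| 20% | 0.20/0.52 = 0.385 | 0.69 |
| 30% | 0.30/0.58 = 0.517 | 0.76 |
| 40% | 0.40/0.64 = 0.625 | 0.81 |

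At f = 20%, p = 0.3 gives 0.73 and p = 0.5 gives 0.67.

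*Softer assumptions.* Let a be the recovery rate among responsive patients, and let the marker be shifted by d SD in them. Write R1 = fa / (fa + (1 − f)p) for the responsive share among the recovered and R0 = f(1 − a) / (f(1 − a) + (1 − f)(1 − p)) for that among the non-recovered. Then AUC = 0.5 + (R1 − R0)(Φ(d/√2) − 0.5).

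- a = 0.95, p = 0.4, d = 2: 0.58, 0.65, 0.70 and 0.74 at f = 10%, 20%, 30% and 40%.
- a = 0.9, p = 0.5, d = 1, f = 10%: R1 = 0.09/0.54 = 0.167 and R0 = 0.01/0.46 = 0.022, so AUC = 0.5 + 0.145 × 0.260 = 0.54.

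In each scenario the AUC among unresponsive patients alone is 0.50.

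**The case against.** Several counter-arguments have force.

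- **Enrollment of awake patients is not shown.** A reader might infer that such patients will be enrolled and will make the EEG look prognostic. The document shows only that nothing excludes them. The Abstract, and the references in the Introduction and Protocol sections to patients who later regain consciousness, point to an unresponsive cohort. All three recordings also presuppose that sedation is restarted. The responsive share could be small.
- **The target is described in two ways.** The Introduction also states the aim for continuously sedated patients, and the Discussion defends the sample as representative of them. A deliberately broad cohort is a legitimate reading. It still leaves the claim about unresponsive patients needing its own evidence.
- **Responding at the interruption is not the endpoint.** A reader might say that recovery of consciousness has already been observed in these patients. The Figure 1 legend and the section on neurocognitive and functional outcomes equate it with the start of CBS testing, which requires being delirium-free and able to do the battery. A patient who responds briefly may still deteriorate or die first.
- **Other outcomes are open at the interruption.** Survival and later cognitive and functional levels are not known then, even for a responsive patient. The AUCs above do not transfer to them.
- **This is a condensed article.** Analysis sets may be defined in the full protocol or SAP, and a Glasgow Coma Scale score is collected without being limited to admission in that list. But eligibility is stated here, and it does not match the claimed use. The only GCS named in an analysis is the one at admission.

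These arguments limit the size and certainty of the problem. They do not remove the mismatch.

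**Conclusion.** The concern holds in a limited form. The criteria allow patients who follow commands off sedation to enter, their status is known before Recording 2, and the described analyses pool them with unresponsive patients. Accuracy for recovery of consciousness may then partly reflect present wakefulness, and may not apply to the unresponsive patients named in the aim.

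The range of 0.61 to 0.81 is an illustration for one outcome. It takes the most favorable case for a wakefulness detector, at an assumed 40% recovery among unresponsive patients and 10% to 40% responsive. Weaker separation and less certain recovery bring it down to about 0.54. The actual bias cannot be sized, because the document does not give the responsive share.

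This should be fixed, but it does not invalidate the cohort: the data remain usable if responsiveness at the interruption is recorded and used.

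**What to change.** 1. Record, in codable form, whether the patient follows commands at the standard-of-care assessment of the recorded interruption. The examination is already part of the sequence, so clinical care does not change.
2. State that classifier performance among patients not following commands at that interruption is the result that supports the claim about unresponsive patients. Report responsive patients separately and the pooled cohort as secondary.
3. Tie the classification to the recorded interruption only. A patient who responded at an earlier interruption but is unresponsive at the recorded one belongs to the stated target and should stay in the main set.
4. Keep all patients enrolled, including for cognitive trajectories.
5. Reconcile the descriptions of the target population in the Abstract, Introduction, Participants and Discussion.

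**Cost.** One recorded item and a short statement of the analysis population. The main prognostic analysis would have fewer patients: 200 × (1 − f) leaves 180, 160 or 120 at an assumed 10%, 20% or 40% responsive. Intervals would be wider by a factor of roughly √(200/n), that is about 1.05, 1.12 or 1.29. The headline accuracy may also be lower.
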